### Sodium glycerophosphate

Sodium glycerophosphate (Fresenius Kabi AG, Bad Homburg, Germany; concentration 1 mmol/ml, ATC-Code: B05XA) is an electrolyte supplement approved and routinely administered for the parenteral treatment of hypophosphatemia especially on intensive care units (ICUs). Phosphate is usually not routinely measured during surgical procedures and is, therefore, not substituted. Accordingly, a hypophosphatemia occurs frequently with an incidence of between 44.8% [23] and 67% [24] and remains undetected, although the unfavourable effects in terms of post-aggression metabolism are well known. The ATP- dependent metabolism strongly relies on phosphate as a substrate, especially during the postoperative phase of major cardiac and abdominal surgery [25, 26]. This leads to a high turnover of phosphate and requires parenteral substitution. Therefore, an intraoperative substitution of phosphate seems reasonable and indicated. It has been shown that an early perioperative substitution of phosphate during liver surgery had a protective effect in terms of cardiorespiratory complication and is, therefore, recommended [27, 28]. Prior to inclusion, all patients will be evaluated regarding contraindications for the use of sodium glycerophosphate (existing chronic kidney disease or renal failure, hyperphosphatemia, hypernatremia or allergic disposition towards sodium glycerophosphate or its components). If none of the above can be detected, the parenteral application of sodium glycerophosphate is uncritical. By contrast to the dosage given on ICUs [29] or according to an estimated basic daily demand of 0.2–0.5 mmol/kg bodyweight (according to the summary of product characteristics) the amount of phosphate given during this trial is low. The maximum infusion rate is 20 mmol phosphate per hour according to the manufacturer and will not be reached. It is expected that during the observation period and due to the substitution, serum phosphate levels will rise around 0.5 mmol/l [22] which will be controlled every 30 min. Since the substituted phosphate gets rapidly metabolized and excess phosphate is excreted in the urine, a severe hyperphosphatemia is not expected [30]. Before initiation of the trial, it was confirmed that Jonosteril® and sodium glycerophosphate are compatible for the intended use. Phosphate will be added to Jonosteril® immediately prior to the application to avoid any potential risk of infection.

## Outcome measures

### Primary objective

The primary objective is to compare two infusion therapy regimes, Jonosteril® + Sodium glycerophosphate (IMP1/IMP2) versus Jonosteril® (IMP1) alone, with the aim to demonstrate superiority of IMP1/IMP2 over IMP1 due to a more stable value of [A^−^] during the observation period of 120 min after the initiation of general anaesthesia.

### Primary endpoint

The primary endpoint is the calculation of [A^−^] in mmol/l according to the Stewart approach of acid-base balance (using equation (2); numerical deviation from reference baseline value around 15 meq/l) and takes place every 30 min over 120 min (time points T1 − T5).

### Secondary objectives

The secondary objectives of the trial are the influence of the distinct infusion therapy regimens on other acid-base parameters, on the onset of PONV, laboratory chemical parameters like electrolytes and their excretion in the urine, as well as hemodynamic stability, monitoring of the vascular barrier (shedding of the glycocalyx), the the use of vasopressors and the safety of the crystalloid preparation in this setting.

Secondary endpoints of the trial are:Serum phosphate levels (ionized in mmol/l, non-ionized in mg/dl, continuous measure from baseline T0 and serial blood draws over a 120-min time frame T1 − T5)Acid-base parameters: pH (numerical), paCO_2_ (mmHg), HCO_3_
^−^ (mmol/l), BE (mmol/l), anion gap (mmol/l); (continuous measure from baseline T0 and serial blood draws over a 120-min time frame T1 − T5)Apparent SID and effective SID (both in mmol/l), Strong Ion Gap (mmol/l), albumin, lactate (ionized in mmol/l, non-ionized in mg/dl, continuous measure from baseline measures T0 and serial blood draws over a 120-min time frame T1 − T5) serum and urine analysis of electrolytes (osmolality in mosmol/l; all other in mmol/l, continuous measure on T6, change from baseline T0)Documentation and analysis of mean arterial blood pressure (MAP) in mmHg, heart frequency in min^-1^, demand of vasopressors (norepinephrine dose in mg/h), stroke volume variation (SVV) in %, central venous pressure (CVP) in mmHg and cardiac output in ml/min (continuous measure from baseline T0 and serial blood draws over a 120-min time frame T1–T5)Assessment of serum creatinine (mg/dl) and urea (mg/dl) as well as calculation of the glomerular filtration rate (ml/min) and creatinine clearance (C_cr_) in ml/min according to the Cockroft-Gault equation [31] as continuous measure on two blood draws at T0 and T6, change from baseline T0)
$$ {\mathrm{C}}_{\mathrm{cr}}=\frac{\left(140-\mathrm{Age}\ \mathrm{in}\ \mathrm{years}\right) \times \mathrm{Mass}\ \left(\mathrm{in}\ \mathrm{kg}\right) \times \left[0.85\ \mathrm{if}\ \mathrm{female}\right]}{72 \times \mathrm{Serum}\ \mathrm{Creatinine}\ \left(\mathrm{in}\ \mathrm{mg}/ dl\right)} $$
Monitoring of the integrity of the vascular barrier function via detection of hyaluronic acid and syndecan-1 (shedding of glycocalyx components) (in ng/ml, continuous measure from baseline T0 and serial blood draws over a 120-min time frame T1–T5)Evaluation and documentation of postoperative nausea and vomiting (descriptive evaluation on day of surgery until postoperative day 3, patients’ account and anaesthesia protocol of surgery, dichotomic measure: yes/no)Onset frequency and intensity of unexpected events: UE/ SUE and SUSARs (critical assessment on day of surgery T1–T5 until postoperative day 3, onset: date, severity score 1–3: mild, moderate, severe, according to detailed injury reporting plan)Necessity of renal replacement therapy (descriptive evaluation, after surgery until postoperative day-3 dichotomic measure: yes/no)

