**Methods/design:**

This is a single-centre, open-label, randomized controlled trial involving two parallel groups of female patients comparing a perioperative infusion regime with sodium glycerophosphate and Jonosteril® (treatment group) or Jonosteril® (comparator) alone. The primary endpoint is to maintain a stable concentration of weak acids [A^-^] according to the Stewart approach of acid-base balance. Secondary endpoints are measurement of serum phosphate levels, other acid-base parameters such as the strong ion difference (SID), the onset and severity of postoperative nausea and vomiting (PONV), electrolyte levels and their excretion in the urine, monitoring of renal function and glycocalyx components, haemodynamics, amounts of catecholamines and other vasopressors used and the safety of the infusion regime.

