## Methods/design

This is a single-centre, phase II clinical trial in patients undergoing major abdominal surgery (Fig. 1). The study follows a prospective, controlled and open design. Initially, the study will begin with a pilot phase of six patients followed by a randomization phase. An overview of the patients’ schedule of activities according to the Standard Protocol Items: Recommendations for Interventional Trials (SPIRIT) figure is provided in Fig. 2.

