### Anaesthesiologic management and postoperative care

All patients will receive anaesthesiologic management according to the institution’s standard. This involves a thoracic epidural anaesthesia in combination with general anaesthesia and the placement of a central venous line and an arterial catheter for haemodynamic monitoring. In case of contraindications to neuroaxial procedures patients will receive general anaesthesia and, postoperatively, patient-controlled analgesia with piritramide. Anaesthesia will be induced with propofol (2 mg/kg), sufentanil (0.4 mg/kg) and rocuronium (0.6 mg/kg) and maintained with propofol and remifentanil or sevoflurane in patients with certain conditions (e.g. cardiopulmonary diseases). The pulmonary ventilation will be standardized in all patients using the volume-controlled mode in order to keep the paCO_2_ at 40 ± 3 mmHg as to have as little influence on acid-base balance as possible (controls are performed using blood gas analysis). The epidural anaesthesia will be continued for at least 3 days and will be combined with nonsteroidal anti-inflammatory drugs. Intraoperative hemodynamic monitoring will be performed using a PulsioFlex monitor with ProAQT® sensor (PULSION Medical Systems SE, Germany). The observation period will be 120 min after initiation of anaesthesia although surgery will take longer in most cases. The administration of the study drug, e.g., sodium glycerophosphate, as well as study-specific blood draws, will take place only during the 120 min of the procedure. Afterwards, the anaesthetist responsible for the patient will continue according to clinical standards. All patients will be transferred from the operating room to the ICU for postoperative surveillance and will be visited by in-hospital postoperative pain management service staff daily.

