#### Data handling and dropouts

INPADS GmbH will perform data management according to the DEGL and DMP. All patients who drop out will be listed, followed-up and monitored. We will document the reason for dropping out and all data registered until then will be included in the analysis. After inclusion of six patients, we will perform an interim analysis. Although dropouts will be very unlikely, due to the design of the study, we will replace the dropout in the case of such an event. Strategies to improve adherence to protocols involve the participation of an investigator (anaesthesiologist) who is responsible for the trial during the initiation of anaesthesia and in the observation period as well as for the completion of checklists in similar format of the CRF. Since patients are under anaesthesia during the intervention, other strategies, such as patient focused techniques, are not intended.

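### The abstract promises PONV severity, but the endpoint is defined as yes/no; with open recording and no masking described, it is also open to reporting bias

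*Protocol article*

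**What the plan says.** The protocol article describes PONV in three places, in three ways.

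- Abstract, Methods/design: a secondary endpoint is "the onset and severity of postoperative nausea and vomiting (PONV").
- Secondary objectives, opening sentence: the regimens' influence "on the onset of PONV" is of interest. Severity is not mentioned.
- Secondary objectives, list of endpoints: the evaluation is a "descriptive evaluation on day of surgery until postoperative day 3", and the source and scale are "patients’ account and anaesthesia protocol of surgery, dichotomic measure: yes/no".

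The next item in that list, on unexpected events, does carry timing and a grade: "onset: date, severity score 1–3: mild, moderate, severe".

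On masking, the abstract calls the trial open-label and the Methods/design section says "The study follows a prospective, controlled and open design". No masking of patients or of those who record PONV is described. Under Data handling and dropouts the article notes the state of the patients: "Since patients are under anaesthesia during the intervention". Under Anaesthesiologic management and postoperative care, study drug is confined to the 120-minute period, and patients "will be visited by in-hospital postoperative pain management service staff daily".

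Trial rationale and hypothesis names fewer cases of PONV as a possible benefit. Analysis procedure says that secondary parameters are analysed descriptively.

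**The concern.** There are two linked problems.

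First, the announced endpoint and the defined endpoint do not match. This is not detail left to a fuller document. The article states the scale, and that scale cannot yield the severity that the abstract promises.

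Second, nausea is subjective, the design is open and a benefit is hoped for. If patients or the staff who question them know the allocation, a difference in PONV between the arms cannot be told apart from a difference in reporting. Describing the result without a test does not remove this, because a biased difference stays biased when it is only described. The article's own facts suggest that the exposure is largely avoidable.

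**Working it through.** **1. The endpoint, place by place**

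| Place | Occurrence | Timing | Severity |
|---|---|---|---|
| Abstract | yes | possibly (onset) | yes |
| Secondary objectives, opening sentence | yes | possibly (onset) | no |
| Secondary objectives, endpoint list | yes | not stated | no |
| For contrast: unexpected events, same list | yes | date | grade 1–3 |

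A yes/no item gives no severity, whether it is asked once or every day. Timing is less clear. A single entry for the whole window would give none, whereas daily entries would give the day of first occurrence. The article does not say which is meant.

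**2. The source.** Two sources are named, the patient's account and the anaesthesia record of surgery. By its name the second belongs to the operation, so the patient's account probably carries most of the period to day 3. That is an inference.

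**3. Whether masking is feasible.** Study drug runs only in the 120 minutes after anaesthesia begins, and patients are anaesthetised during it. They therefore need not learn the allocation from the infusion. The team giving the infusion can stay open while the patient and the PONV recorder do not.

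**4. The plan's own number.** The only figure needed here is 21 per arm. It was set for the primary endpoint, and no figure is given for PONV. Inputs are a difference of 0.60 × 2.67 = 1.602 mmol/l, an SD of 1.8 mmol/l, a 5% level (taken as two-sided) and 80% power. A two-sample t test then needs 20.8, rounded up to 21 per arm, with power 80.3%. The figure reproduces.

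**5. Scale of a possible bias (assumed rates; the documents give none).** Suppose there is no true effect, the true PONV rate is p, and a fraction b of the cases in one arm go unreported. The apparent risk difference is then p × b.

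- p = 0.30, b = 0.10: 0.30 × 0.10 = 0.03, or 3 points (21 × 0.03 = 0.6 patients).
- p = 0.50, b = 0.30: 0.50 × 0.30 = 0.15, or 15 points (21 × 0.15 = 3.2 patients).

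**6. What the yes/no comparison could show even without bias.** Power to detect a halving of PONV with 21 per arm, two-sided 5%, control rates again assumed:

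| Control rate | Halved to | Normal approximation | Fisher's exact test |
|---|---|---|---|
| 30% | 15% | 21% | 13% |
| 40% | 20% | 29% | 19% |
| 50% | 25% | 38% | 26% |
| 60% | 30% | 50% | 36% |

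No test of PONV is planned, so these values are context only. They show that a spurious difference of a few patients would weigh heavily in so small a comparison.

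**The case against.** The strongest reply is that little hangs on this. PONV is one of many secondary endpoints, all analysed descriptively, in an exploratory phase II trial. The rationale calls a reduction possible and no more. The primary endpoint is calculated from laboratory values, which patient reporting cannot move. All of this stands, and it limits the weight of the point. It does not resolve the conflict over severity.

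Several stronger readings are tempting, and the documents do not support them:

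- *That onset is lost as well.* The article elsewhere uses the word loosely for occurrence, and it does not say that there is only one entry per patient. Only severity is clearly in conflict.
- *That PONV rests solely on the reports of unblinded patients.* A second source is named. Open-label suggests that patients may know their arm, but the article does not say that they are told.
- *That the pain service is independent of the infusion team.* The article says only that its staff visit daily.
- *That masking would cost nothing.* The documents do not address its cost. The trial is already recruiting and changes must go to the authorities.
- *That 1/21 = 4.8 percentage points measures the bias.* It is the weight of one patient in an arm of 21. It does not say how many reports would be swayed, or in which direction.

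It is also fair to say that a full set of nausea scales, episode counts and time-to-event summaries would go further than the discrepancy requires.

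**Conclusion.** The point holds in a limited form. The abstract announces a severity endpoint that the stated yes/no measure cannot deliver. Separately, a partly self-reported secondary outcome is to be recorded in an open trial with no masking described, although the patients' anaesthesia makes masking of patient and recorder feasible. The severity mismatch rests on the text alone. The exposure to bias rests on the ordinary meaning of open-label and on the patient's account carrying most of the postoperative window. The range of 3 to 15 points rests wholly on assumed rates and shows scale; it does not estimate the bias. The primary endpoint is not touched.

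**What to change.** For patients still to be enrolled:

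1. Do not disclose the allocation to the patient, or to the person recording PONV, until the day-3 assessment is complete. State this in the protocol.
2. At the existing daily visits, record a simple PONV severity grade and the day of first occurrence. The three-level score already used for unexpected events would serve. Confirm that the visits continue to day 3, because the article does not say how long they last.
3. Word the endpoint identically in the abstract, the objectives and the endpoint list, and say whether onset means occurrence or timing.

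If this is not wanted, remove severity from the stated endpoint and report PONV as unblinded incidence only.

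The cost is a CRF and protocol amendment in a trial already recruiting, notified to the authorities; a question or two more per visit; and keeping the allocation out of the notes that the PONV recorder uses. Patients already assessed will lack the graded, masked data, so their results should be shown separately from those collected under the new procedure.

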**Fig. 2 Fig2:**
[figure not shown]
Patient schedule of activities according to the Standard Protocol Items: Recommendations for Interventional Trials (SPIRIT) figure. *SID* Strong Ion Difference, *SUEs* serious unexpected events, *SUSARS* severe unexpected serious adverse event, *UE* unexpected events, *UO* urinary output

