#### Analysis procedure

The primary objective of the study is to show that during the observation period of 120 min the mean values of [A^−^] display a lower deviation in the treatment group when compared to the control. We will evaluate normal distribution using the Kolmogorov-Smirnov test. To test for differences between two study groups with normally distributed data, a two-sample *t* test will be used. In order to evaluate differences of [A^−^] within one study group over time, we will perform a RM-ANOVA with a *t* test for paired samples as post hoc. We will analyse data that does not follow a normal distribution using the Friedman test. Level of significance for all calculations is defined at 5%. We will analyse secondary parameters descriptively and calculate mean, number, minimum, maximum, 1st quartile, 3rd quartile, mean standard error and standard deviation (SD) (method of aggregation: continuous). Further analyses and testing procedures can be defined at a later stage. The primary statistical analysis is based on the “intention-to-treat” principle. Safety data (UE, SUE, SUSARs) will be analysed descriptively in all groups at least every 12 months.

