## Abbreviations

AE: Adverse event
ASA: American Society of Anaesthesiologists’ performance status classification system
CRF: Case Report Form
CRO: Contract Research organizations
DEGL: Data entry guideline
DMP: Data management plan
ECG: Electrocardiography
GFR: Glomerular filtration rate
Hb: Haemoglobin
ICU: Intensive care unit
IMP: Investigational medicinal product
ITT: Intention-to-treat
IV: Intravenous
SAE: Serious adverse event
SDP: Sponsor-delegated person
SD: Standard deviation
SUE: Severe unexpected event
SUSAR: Severe unexpected serious adverse event
SVV: Stroke volume variation
UE: Unexpected event

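### The safety event count is worded as unexpected events only, and the article's safety terms disagree on severe versus serious

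*Protocol article*

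**What the plan says.** Under Secondary objectives, the Protocol article names safety as an aim and sets the event endpoint as "Onset frequency and intensity of unexpected events: UE/ SUE and SUSARs". It runs from the day of surgery to postoperative day 3. Each event gets a "severity score 1–3: mild, moderate, severe, according to detailed injury reporting plan"; that plan is not shown.

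Analysis procedure uses the same three categories: "Safety data (UE, SUE, SUSARs) will be analysed descriptively in all groups at least every 12 months".

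The terms are expanded in two places:

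- Abbreviations gives "UE: Unexpected event", "SUE: Severe unexpected event" and "SUSAR: Severe unexpected serious adverse event".
- The Fig. 2 legend expands SUEs as "serious unexpected events". It expands SUSAR in the same words as Abbreviations.

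Abbreviations also lists AE and "SAE: Serious adverse event". Neither is used in any endpoint or analysis in the visible text.

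**The concern.** An event endpoint meant to describe safety should count harms whether or not anyone foresaw them. Here the endpoint, the analysis and both glossaries all use *unexpected*, so this is the stated rule and not a detail left to another document.

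Two features make the wording matter. First, the trial is open-label, so whoever judges whether an event was expected can know the arm. Second, what is foreseen differs by arm. The article forecasts a phosphate rise of about 0.5 mmol/l with substitution (Sodium glycerophosphate), and expects low phosphate to be avoided in the treatment group in contrast to the control group (Trial rationale and hypothesis). A filter on expectedness could therefore remove different events from the two arms.

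The severe/serious conflict is a separate problem. Intensity and seriousness are different classifications, and two people working from different parts of the article would file the same event differently.

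**Working it through.** No calculation in the plan bears on this point, so the check is a comparison of text.

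**Step 1. The terms side by side**

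| Place | UE | SUE | SUSAR |
|---|---|---|---|
| Secondary objectives | unexpected | not expanded | not expanded |
| Fig. 2 legend | unexpected | *serious* and unexpected | severe, unexpected, serious |
| Abbreviations | unexpected | *severe* and unexpected | severe, unexpected, serious |
| Analysis procedure | not expanded | not expanded | not expanded |

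Neither expansion of SUSAR contains a suspected relation to a study product.

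**Step 2. Classify events under the literal wording**

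Take three yes/no attributes: foreseen, severe (score 3) and serious. They give 2 × 2 × 2 = 8 types of event.

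| Foreseen | Severe | Serious | Fig. 2 legend | Abbreviations |
|---|---|---|---|---|
| No | No | No | UE | UE |
| No | No | Yes | SUE | UE |
| No | Yes | No | UE | SUE |
| No | Yes | Yes | SUE, SUSAR | SUE, SUSAR |
| Yes | any | any (4 types) | none | none |

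- The 4 foreseen types have no category under either reading.
- Of the 4 unforeseen types, 2 change category with the glossary used.
- SUSAR takes in the one type that is unforeseen, severe and serious. It does so whether or not a study product is suspected, so it does not separate product-related events from surgical complications.

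These are types of event, not frequencies. The table shows where the wording fails, not how often.

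**Step 3. What is captured elsewhere**

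- Serum phosphate at T0–T5; sodium, potassium, calcium, magnesium and osmolality at T1–T5 (Table 1).
- Creatinine, urea and GFR at T0 and T6 (Table 1).
- PONV and need for renal replacement therapy, yes/no to postoperative day 3 (Secondary objectives).
- Central venous pressure and stroke volume variation at T1–T5 (Table 1).
- Analysis procedure includes the minimum and maximum among the summaries of secondary parameters, so extreme laboratory values would be visible.

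**Step 4. What that leaves**

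Study-specific blood draws are confined to the 120 minutes (Anaesthesiologic management and postoperative care). The endpoint list also puts electrolytes at T6, for which the visible text gives no clock time. The event endpoint runs to day 3. For a foreseen disturbance after the infusion, or a foreseen clinical event without its own endpoint, the event count may be the main route of capture.

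**Step 5. Does the text call the main harm expected?**

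Only in part. The phosphate rise of about 0.5 mmol/l is forecast as an effect of substitution, not declared a harm. Severe hyperphosphataemia is not anticipated (Sodium glycerophosphate), so it would be an unexpected event and would be counted. The gap concerns foreseen and lesser events.

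**The case against.** The strongest reply is that this is a wording slip in a condensed article. AE and SAE in Abbreviations suggest that UE and SUE may have been meant as adverse and serious adverse events. No sentence says that expected events go unrecorded, and the operative definitions may be in the full protocol or the reporting plan. The main laboratory and renal harms are measured in any case.

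Much of this stands, and it limits the point. Four stronger readings are tempting, and the documents do not support them:

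- *That severity has replaced seriousness as the criterion.* The Fig. 2 legend says serious. The article contradicts itself and settles nothing, and nowhere does it say that a score of 3 makes an event an SUE.
- *That none of the study fluids' risks would be counted.* Severe hyperphosphataemia would be. Oedema, hyperhydration, hypernatraemia, hypocalcaemia and hyperkalaemia appear as contraindications or exclusion criteria, not as declared expected effects.
- *That expedited reporting would go wrong.* The article states no such rule, refers events to a plan that is not shown, and commits the trial to the Clinical Trials Directive and ICH-GCP.
- *That the safety comparison is biased towards no difference, or that safety could not be concluded.* No event data support either. Because different things are foreseen in each arm, even the direction of any distortion is open.

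The reply does not remove the core. The same word appears in the endpoint and in both glossaries, and the analysis repeats its categories. If it is a slip for *adverse*, the published endpoint is still wrong as it stands. The severe/serious conflict is on the page whatever the unseen documents say.

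**Conclusion.** The point holds in a limited form. As written, the event endpoint and its analysis cover unexpected events only, SUE has two incompatible expansions, and SUSAR lacks any suspected relation to a study product. These are stated rules that need correction, not missing detail.

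The size of any under-counting cannot be given, because the article states no adverse event rates and no list of expected events. It is a risk that depends on the literal wording being followed. If the full protocol or reporting plan already uses adverse and serious adverse events, the remaining fault is that the published text does not match it. The primary endpoint and the sample size are unaffected. The correction is worth making because safety is a named objective, the trial is open-label and rewording is cheap.

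**What to change.** Reconcile Secondary objectives, the Fig. 2 legend, Analysis procedure and Abbreviations with each other and with the reporting plan:

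1. Replace UE and SUE with adverse events and serious adverse events, collected over the period already stated and regardless of expectedness.
2. Keep the 1–3 score as a grade of intensity, and record seriousness as a separate item.
3. Define SUSAR as a serious, unexpected event suspected to be related to a study product, and use that definition everywhere.
4. Tabulate adverse and serious adverse events by arm.

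Listing out-of-range laboratory values as events as well is a matter of preference and is not needed to close the gap.

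The cost is wording in four places, matching CRF labels, and a few more, mostly minor, events to record in 48 patients (6 pilot + 42 randomized). No new procedures or samples are needed.
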